#### Exclusion criteria

Residents who are pregnant, participants of other clinical trials or plan to leave the area before end of the study period will be excluded.

### Sample size calculation and recruitment

The sample size was calculated by assuming p < 0.05 as the significance level, 80% power and 1 to 1 as the ratio of unexposed to expose in sample. The calculation was carried by using the OpenEpi version 2.3.1 [15]. On the assumption of an SD of 15 mmHg and 30% drop out, a sample size of 160 participants per group is required to detect the effect size of systolic blood pressure 5.4 mm Hg. The effect size used to calculate the sample size was based onthe result of a previous similar study[16].

Universal sampling method will be used to recruit the study participants. The 431 residents of the selected community housing complexes who were diagnosed as (stage 1 to 3) hypertension will be invited to the study. We will take all participants which fit with inclusion criteria and willing to participate to the study so that actual participants may be more than calculated sample size.

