**Methods:**

The study is a two armed, parallel group, un-blinded, cluster randomized controlled trial undertaken within lower income areas in Kuala Lumpur. Two housing complexes will be assigned to the intervention group and the other two housing complexes will be allocated in the control group. Based on power analysis, 320 participants will be recruited. The participants in the intervention group (n = 160) will undergo three main components in the intervention which are the peer support for home blood pressure monitoring, face to face health coaching on healthy diet and demonstration and training for indoor home based exercise activities while the control group will receive a pamphlet containing information on hypertension. The primary outcomes are systolic and diastolic blood pressure. Secondary outcome measures include practice of self-blood pressure monitoring, dietary intake, level of physical activity and physical fitness.

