### Data management and analysis

The data analysis will be done by using Stata software (version 11: StataCorp). Bivariate analysis such as Chi-square tests (for dichotomous and categorical variables), t test and ANOVA (for continuous and normally distributed variables) and Mann-Whitney-U test (for continuous variable with skewed distribution) will be applied to compare the two groups with respect of socio-demographic characteristics, number of clinic visits, practice of self-blood pressure monitoring, blood pressure at the time of enrolment, dietary intake, level of physical activity and fitness.

The primary outcome, change in systolic and diastolic blood pressure at six months and twelve months will be compared between and within the groups by using t test and ANOVA. If there are some differences in group characteristics, it will be adjusted by performing multivariate analysis of variance (MANOVA).

Since the secondary outcomes such as numbers of self-blood pressure monitoring, dietary intake, body composition (BMI, fat percentage, waist and hip circumference ratio), level of physical activity and physical fitness are also continuous variables, these will be examined as per primary outcome. The normality of the continuous variables will be checked before analysis and proper transformation will be done if the data is not normally distributed. The level of statistical significance will be set at p < 0.05.

In order to calculate nutrient intake, Nutritionist Pro™ Diet Analysis software will be used to analyse the diet record. It will focus mainly on energy, protein, fat, carbohydrate, sodium, dietary fibre and others. Based on the 7 days diet histories, the average energy consumed with macronutrients (e.g: Energy intake (kcal), protein (g), fat (g), saturated fat (g) and others) and micronutrients (e.g: calcium (mg), iron (mg), vitamins and minerals) value will be calculated. All nutrient intakes will be transferred to the Stata software for final data analysis.

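### At the planned 30% dropout, 160 per group leaves 112 completers and about 77% power, not the stated 80%, even before clustering

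*Protocol article*

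**What the plan says.** The section on sample size calculation and recruitment gives the inputs. On error rates: "The sample size was calculated by assuming p < 0.05 as the significance level, 80% power". On allocation: "1 to 1 as the ratio of unexposed to expose in sample". On variability, loss and result: "On the assumption of an SD of 15 mmHg and 30% drop out, a sample size of 160 participants per group is required". The target is the number "required to detect the effect size of systolic blood pressure 5.4 mm Hg".

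The Methods paragraph of the abstract carries the total forward: "Based on power analysis, 320 participants will be recruited".

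Neither the number needed before dropout nor the dropout formula is printed. Sidedness is not given either; the analysis section says only "The level of statistical significance will be set at p < 0.05". The sample size section adds that all 431 identified residents with hypertension will be invited and that everyone eligible and willing will be taken, so enrolment might exceed the calculated number.

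**The concern.** An allowance for dropout should leave the required number of participants after the losses. If a fraction d is lost, the evaluable number must be divided by 1 - d. Multiplying by 1 + d gives too few, and at d = 30% the gap is no longer trivial. The stated 160 looks like the product of that multiplication.

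If so, the article claims a protection that it does not have. Readers would take 160 per group as holding 80% power after 30% loss, and 320 as what the power analysis requires. The number is also the base to which any correction for cluster randomisation would be applied, so an error here carries forward.

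**Working it through.** **Inputs** (all from the sample size section, except sidedness): significance level 0.05; power 80%; ratio 1:1; SD 15 mmHg; difference 5.4 mmHg; dropout 30%; 160 per group. The test is assumed two-sided. Participants are treated as independent, as the stated inputs imply.

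**1. Evaluable number per group**

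n = 2 x (z_0.975 + z_0.80)^2 x SD^2 / difference^2
= 2 x (1.960 + 0.842)^2 x 225 / 29.16 = 121.1, so 122.

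The exact t-test calculation gives 122.1.

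**2. Reproducing the stated 160**

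| Variant | Evaluable n | No inflation | n x 1.3 | n / 0.7 |
|---|---|---|---|---|
| Two-sided | 122 | 122 | 158.6 (159) | 174.3 (175) |
| One-sided | 96 | 96 | 124.8 (125) | 137.1 (138) |

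Only the two-sided calculation with n x 1.3 comes near 160, and it still needs a small rounding up from 159. Dividing the t-test figure by 0.7 gives 174.4, which is also 175.

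**3. What 160 per group delivers at 30% dropout**

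- Completers per group: 160 x 0.7 = 112, which is 10 short of 122.
- Power: Phi(5.4 / (15 x sqrt(2/112)) - 1.960) = Phi(2.694 - 1.960) = Phi(0.734) = 76.9%. The t test gives 76.5%.
- Difference detectable with 80% power: 2.802 x 15 x sqrt(2/112) = 5.62 mmHg, against 5.4 stated.

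**4. Dropout that 160 per group can absorb at 80% power**

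(160 - 122) / 160 = 38 / 160 = 23.75%, about 24%.

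**5. Number that follows from the stated assumptions**

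122 / 0.7 = 174.3, so 175 per group or 350 in total. That is 15 per group and 30 overall above the stated figures.

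**The case against.** The arithmetic is not in dispute. The case on the other side is about what can be asserted and how much it matters.

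- **The formula is not printed.** This is correct. The n x 1.3 step is an inference. The shortfall does not rest on it: 112 completers and about 77% power follow from the stated inputs however 160 was reached.
- **Sidedness is not stated.** This is also correct. A one-sided test would have 85% power at 112 per group, with no shortfall. But one-sided calculations give 125 or 138 after inflation, not 160, so two-sided is the reading consistent with the article's own result.
- **The loss is small.** It is about 3 percentage points. An SD of 14.4 instead of 15 would restore 80% power at 112 per group, so the gap lies within the uncertainty of the planning SD. This limits the weight of the point, but the printed statement remains wrong for the SD it names.
- **Recruitment may exceed the target.** The section allows for this but commits to nothing above 160. Of the 431 invited, 320 is 74% and 350 is 81%, and all must still meet the eligibility criteria. Possible over-recruitment does not make the stated power correct.
- **Clustering dominates.** This stands, as a separate and larger matter. Two complexes per arm are randomised, and the sample size section states no design effect. The documents give no intracluster correlation. Assuming 0.005 to 0.02, equal clusters and design effect 1 + (m - 1) x ICC, where m is the number of completers per complex, 112 completers per arm (m = 56) give design effects of 1.275 to 2.1 and power of about 66% to 46%. With 122 per arm (m = 61), power is about 69% to 47%. These figures still ignore the further loss from having only four clusters. Extra participants within the same complexes therefore buy little, and neither 77% nor 175 should be printed without saying that clustering is left out.

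**Conclusion.** The point holds. Taken together, 80% power, 30% dropout and 160 per group are inconsistent with an SD of 15 mmHg and a difference of 5.4 mmHg. At 30% dropout the power is about 77%, and 80% power survives only up to about 24% dropout. Keeping both the 30% and the 80% requires 175 per group.

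This rests on a two-sided 5% test, which is assumed, and on independent participants. Any positive intracluster correlation lowers the true power further, so 77% is an upper figure for this design under the stated inputs. The error is modest, does not bias the analysis and leaves the design unchanged. It should be corrected because a stated power and a stated sample size are wrong as written.

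**What to change.** Correct the sentence in the sample size section. It should state that the test is two-sided (if that was intended), give the 122 evaluable participants needed per group, and show how dropout was allowed for. Then use one of these:

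- 160 per group keeps 80% power up to about 24% dropout; or
- with 160 per group and 30% dropout, power is about 77%.

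Either statement must say that it is before any allowance for clustering. Both leave the 320 in the abstract unchanged and need no extra enrolment. The cost is one sentence and a slightly less favourable claim.

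If 30% dropout and 80% power are both to be kept, the individual-level figure becomes 175 per group and the abstract total 350. That should not be offered as a sufficient target for this cluster trial, because clustering remains unaddressed. The recruitment rule already takes every eligible and willing resident, so none of the three options requires a new one.

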### Study design and setting

The study is a two armed, parallel group, un-blinded, cluster randomized controlled trial undertaken within lower income areas in Kuala Lumpur. There are six community housing complexes in the study area. Of these four housing complexes will be randomly selected and allocated (1:1) to the intervention and control arm (Figure 1).

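### The sample size comes from an individually randomised formula with no design effect, so four housing complexes do not deliver the stated 80% power for 5.4 mmHg

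*Protocol article*

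**What the plan says.** Under Study design and setting, the article describes a two-arm "cluster randomized controlled trial undertaken within lower income areas in Kuala Lumpur". The Abstract (Methods) fixes the number of clusters: "Two housing complexes will be assigned to the intervention group and the other two housing complexes will be allocated in the control group".

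The section Sample size calculation and recruitment lists these inputs: "The sample size was calculated by assuming p < 0.05 as the significance level, 80% power", then "1 to 1 as the ratio of unexposed to expose in sample", then "On the assumption of an SD of 15 mmHg and 30% drop out". It concludes that "a sample size of 160 participants per group is required to detect the effect size of systolic blood pressure 5.4 mm Hg". It names the software: "The calculation was carried by using the OpenEpi version 2.3.1". It mentions no ICC, design effect, cluster size or number of clusters.

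The same section says that all 431 identified residents will be invited, so enrolment may exceed 320. Data management and analysis compares blood pressure change between arms by t test and ANOVA, with MANOVA if the groups differ in their characteristics. No cluster term is named.

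**The concern.** The unit of allocation is the housing complex, but the calculation treats each resident as independently allocated. Two things are lost. Residents of one complex tend to resemble each other, which reduces the information per person. With two complexes per arm there is also very little replication from which to estimate variation between complexes.

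Zero correlation is a poor default here. Under Intervention, peer groups of five are formed from neighbours and the dietary coaching is given in group sessions.

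The article does not merely leave the point unmentioned. It asserts that 160 per group is what 80% power requires. A null result could then be read as evidence against a 5.4 mmHg effect that the trial had little chance of detecting. A positive result would rest on a test that ignores the clusters.

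**Working it through.** **Inputs from the article:** difference δ = 5.4 mmHg, SD = 15 mmHg, α = 0.05 (taken as two-sided, since one-sided does not reproduce the stated number), power 80%, 1:1 allocation, 30% dropout, 160 per arm, two complexes per arm. **Assumed, because the article gives none:** the ICC, over 0 to 0.05. Equal complex sizes are also assumed.

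**1. Reproduce the stated number.**
n = 2 × (1.96 + 0.8416)² × 15² / 5.4² = 121.1, so 122 per arm (123 with the t distribution).
122 × 1.30 = 158.6, so 159; 123 × 1.30 = 159.9, so 160.
The stated 160 is used up by the individual-level formula and the dropout multiplier. Nothing is left for a design effect above 1.

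**2. Separate the dropout component.** Allowing for 30% loss requires n / 0.7, which gives 175 to 176. With 160 enrolled, 160 × 0.7 = 112 remain, and power without any clustering is 76.9%. This small shortfall is not due to clustering.

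**3. Add clustering.** With 112 completers per arm, m = 112 / 2 = 56 per complex.
- Design effect: DE = 1 + (56 − 1) × ICC
- Effective sample per arm: 112 / DE
- SE = 15 × √(2 × DE / 112)
- Large-df power = Φ(5.4 / SE − 1.96)
- 2-df power: noncentral t with noncentrality 5.4 / SE, critical value 4.303, df = 4 clusters − 2 arms
- Detectable difference at 80% power (large df) = 2.80 × SE

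| ICC (assumed) | DE | Effective n per arm | Power, large df | Power, 2 df | Detectable difference, large df (mmHg) |
|---|---|---|---|---|---|
| 0 | 1.00 | 112 | 76.9% | 33% | 5.6 |
| 0.001 | 1.06 | 106 | 74.6% | 32% | 5.8 |
| 0.005 | 1.28 | 88 | 66.5% | 28% | 6.3 |
| 0.01 | 1.55 | 72 | 58% | 24% | 7.0 |
| 0.02 | 2.10 | 53 | 46% | 20% | 8.1 |
| 0.05 | 3.75 | 30 | 28% | 14% | 10.9 |

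Example at ICC 0.02: SE = 15 × √(2 × 2.10 / 112) = 2.90; 5.4 / 2.90 = 1.86; Φ(1.86 − 1.96) = 46%.

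**4. Can more residents repair it?** With two complexes per arm, the evaluable number needed for 80% (large df) is 121.1 × (1 − ICC) × 2 / (2 − 121.1 × ICC).
- ICC 0.005: 173 evaluable, so 173 / 0.7 = 248 enrolled per arm, 496 in total. This exceeds the 431 invited.
- ICC 0.01: 305 evaluable, 436 enrolled per arm.
- ICC of 2 / 121.1 = 0.0165 or more: no number suffices.

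With unlimited residents the SE falls only to 15 × √ICC. At ICC 0.02 that is 2.12, giving 72% (large df) and about 31% (2 df).

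**5. What the planned test does instead.** A t test that ignores the complexes has a type I error of about 2 × [1 − Φ(1.96 / √DE)]. With m = 56 this is 8%, 12%, 18% and 31% at ICC 0.005, 0.01, 0.02 and 0.05, against a nominal 5%.

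**The case against.** The strongest reply is that the power figures above are not those of the planned test. The individual-level t test with 112 per arm would reject at a true 5.4 mmHg in about 72%, 69% and 66% of trials at ICC 0.01, 0.02 and 0.05. This is correct, but it is no defence. Those rejections come from a test whose false-positive rate is 12%, 18% and 31%, and power is meaningful only at the level the protocol claims, 5%. What stands is that the power figures belong to a cluster-valid test and must be labelled so, and that the sample size paragraph cannot be corrected in isolation from the analysis section.

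Second, the ICC is assumed, and the ICC of a change in blood pressure may differ from that of a level. This stands for the size of the loss. At ICC 0.001 the large-df loss from clustering is small (76.9% to 74.6%). The direction is not in doubt, and the 2-df figures are low at every ICC.

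Third, 112 completers is pessimistic, because enrolment may exceed 320. Applying 30% loss to 431 leaves about 150 per arm (431 × 0.7 / 2), and large-df power is then 76%, 66% and 51% at ICC 0.005, 0.01 and 0.02. If all 431 enrolled with no loss (about 215 per arm), it is 85%, 74% and 56%. So 80% can be reached under a large-df test when the ICC is very small and recruitment is near complete. The 2-df test does not reach it even then (39%, 32% and 24%). The article also attaches its 80% claim to 160 per group, not to these larger numbers.

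Finally, a journal article condenses a fuller protocol. That does not help here: the printed inputs account for the whole of the 160.

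**Conclusion.** The concern holds. The 80% power stated for 5.4 mmHg belongs to an individually randomised trial and not to this one. At 160 enrolled per arm with 30% loss, power with a cluster-adjusted large-df test is 58%, 46% and 28% at assumed ICCs of 0.01, 0.02 and 0.05. With the 2 degrees of freedom of a cluster-level test it is 24%, 20% and 14%, and no more than 33% even if the ICC is zero. If every one of the 160 per arm were evaluable, 2-df power would still be at most 43%.

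The size of the shortfall rests on the assumed ICC, equal complex sizes, the article's SD of 15 mmHg and its 30% loss. The absence of a design effect rests on the article's own numbers alone. The main limit is the number of complexes, not the number of residents, and the article reports only six complexes in the area.

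**What to change.** In Sample size calculation and recruitment, remove the unqualified statement that 160 per group gives 80% power for 5.4 mmHg, and replace it with what 320 residents in four complexes deliver:

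- State that the calculation (122 to 123 per arm, times 1.30) made no allowance for clustering, and that 30% loss from 160 leaves 112 per arm.
- Give an ICC range with its justification, the design effect at 56 completers per complex, and the resulting power or detectable difference, as in the table above. Include values below 0.01.
- Name the test to which each power figure refers, and show the 2-df result beside the large-df result. Cross-refer to Data management and analysis, where the t test and ANOVA name no cluster term, so that the stated power and the planned test agree.
- Describe the trial as estimating the effect with limited cluster replication, and say that a non-significant result does not exclude a 5.4 mmHg difference.

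This takes one paragraph and a cross-reference. It needs no increase in enrolment and no added complexes. The cost is a less favourable stated power.

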### Intervention

The intervention is developed based on Social Cognitive Theory which includes social support, self-regulation and self-efficacy [17]. There will be three main components in the intervention i) Peer support for home blood pressure monitoring, ii) Face to face health coaching on healthy diet iii) Demonstration and training for indoor home based exercise activities.

Peer support groups, consisting of five persons per group will be formed based on the proximity of the residences. An Omron digital blood pressure monitor (HEM-7111) will be distributed to each group and participants will be trained by a state registered nurse on how to measure blood pressure and record the blood pressure reading in a log book.

Dietary assessments of individual participants will be conducted by three dietitians using 7 days diet histories. These dietitians will be randomly assigned to participant groups to assess the food intake. The same principal dietitian will conduct six sessions of health coaching to the participants in the group. The content of health coaching will include diet modification according to the DASH (Dietary Approaches to Stop Hypertension)diet [7,18] and reduction of sodium intake. The sodium reduction approach that will be used in this study is by educating the participants to use herbs and spices in their cooking and by reducing the table salt usage. Healthy cooking demonstration and practices of reading food label will also be included in the sessions of health coaching. High in sodium foods will be encouraged to be minimised. The health coaching materials to the intervention groups are the same whilst control will receive healthy diet leaflet at the beginning of the study. After completing the intervention, the three dietitians will do the post intervention dietary assessment using the 7 days diet histories.

Exercise demonstrations and training will be conducted by a certified trainer from the sport medicine department. The exercise demonstration will focus on strengthening and flexibility exercise. The participants will be recommended to do low to moderate level physical activity and exercise minimum 150 minutes per week. Brisk walking will be also recommended as aerobic exercise. An exercise compact disc (CD) will be provided to the study participants as a guide to do exercise on their own. The participants will also be trained to record their physical activity in a log book. A Body Mass Index (BMI) calculator will be provided to help them to check their own BMI.

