**Figure 1 F1:**
[figure not shown]
Flow of participants in the intervention and control arm

The intervention group will receive training on self-measurement of blood pressure, health coaching on healthy diet, training for indoor exercise activities and the use of Body Mass Index (BMI) calculator. Participants in the control group will receive a BMI calculator and a pamphlet developed by the study team which includes brief information on hypertension, healthy diet and physical activity.

Residents of the selected community housings who were diagnosed as having (stage 1 to stage 3) hypertension by medical professionals will be recruited as participants for the study. The potential participants will be identified based on the household survey data which was carried out by the 'PARTNER' study team from the University of Malaya. This survey was a cross-sectional design and conducted between February to November 2012. Altogether, 833 households were recruited from total 4726 households of four Community Housing Projects by using simple random sampling method. From 833 households, 431 individuals with hypertension were identified.

Inclusion and exclusion criteria of the study are as follows.

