One of the expert recommendations to improve hypertension management in Asia is to increase awareness of hypertension, enhance treatment adherence and promote home blood pressure monitoring [4]. Positive impact of self-monitoring of blood pressure on treatment adherence and reduction of blood pressure has been demonstrated in high income countries [11,13,37,38].

However, to obtain a blood pressure monitor is a big challenge since more than half of our study population have an average household income less than 2,000 MYR which equivalent to (USD 605). The purchase of a reliable quality digital blood pressure monitor would cost about 10% of household income which is generally considered as catastrophic health care expenditure [39]. Our study proposed a solution to overcome the issue of unaffordability to obtain the blood pressure monitor. Since there is an existing social network in the community and practice of sharing resources, we formed a peer support group and provided a digital blood pressure monitor. We believed that it would encourage the sharing of knowledge on hypertension, disease progress and practice of self-blood pressure monitoring among the participants. Although it is expensive for a single person to purchase a blood pressure monitor for his/her own, sharing equipment among peer group members would be affordable and a practical solution for a low income community who lives the same community housing complex.

We expected that after completing intervention, the participants of our study could benefit by increasing awareness of healthy diet and physical activity, adopting healthy life style and improving self-management of hypertension. The proposed intervention would ensure the self-efficacy and self-regulation of regular blood pressure monitoring, healthy diet choice, and maintaining physical activities and exercise with peer social support. There would be a promising possibility that our intervention is widely replicable and adopted as a model of community based approach for combating hypertension in low and middle income countries.

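### The planned t test and ANOVA treat intervention participants as independent although they are put in peer groups of five that exist in that arm only; this is real but secondary to the ignored clustering by housing complex

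*Protocol article*

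**What the plan says.** All places are in the protocol article.

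- **Intervention:** "Peer support groups, consisting of five persons per group will be formed based on the proximity of the residences". One device serves each group: "An Omron digital blood pressure monitor (HEM-7111) will be distributed to each group".
- **Discussion:** "we formed a peer support group and provided a digital blood pressure monitor". The stated hope is that members will share knowledge and the habit of self-monitoring, so influence between members is an intended mechanism.
- **Text under Figure 1:** "Participants in the control group will receive a BMI calculator and a pamphlet developed by the study team". No peer groups are described for controls.
- **Study design and setting:** "Of these four housing complexes will be randomly selected and allocated (1:1) to the intervention and control arm". That gives two complexes per arm.
- **Sample size calculation and recruitment:** "On the assumption of an SD of 15 mmHg and 30% drop out, a sample size of 160 participants per group is required", for a 5.4 mmHg systolic difference, "assuming p < 0.05 as the significance level, 80% power and 1 to 1 as the ratio of unexposed to expose in sample". No design effect appears at any level.
- **Data management and analysis:** change in systolic and diastolic pressure at six and twelve months "will be compared between and within the groups by using t test and ANOVA". I read the groups here as the trial arms. MANOVA is reserved for imbalance in group characteristics. Continuous secondary outcomes are to be examined in the same way as the primary. Neither peer group nor housing complex enters any named analysis.

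**The concern.** Members of a peer group are close neighbours who share a monitor and are meant to influence one another. Their changes in blood pressure, diet, activity and fitness may therefore be more alike than those of two members of different groups. Controls have no counterpart, so the design is partially nested: individuals in one arm, groups of five in the other.

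A t test or ANOVA on individuals counts the intervention arm as 160 independent observations when it holds about 160/5 = 32 groups. If outcomes are positively correlated within groups, the standard error is too small. The between-arm comparison takes this error from one arm only. The within-arm comparison for the intervention arm takes it in full, with no control arm to dilute it.

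**Working it through.** **Reproducing the plan's figure.** Inputs from the sample size section: SD 15 mmHg, difference 5.4 mmHg, alpha 0.05 (taken as two-sided, since sidedness is not stated), power 80%.

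n per arm = 2 × (1.960 + 0.842)² × 15² / 5.4² ≈ 121.1, rounded up to 122. Then 122 × 1.3 = 158.6, or 159, which agrees with the stated 160. (Dividing by 0.7 would give 175; that is a separate matter.) The stated figure is thus reached with independent participants and no allowance for correlation.

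**Peer-group correlation under the planned tests.** The ICC is assumed, as the documents give none. Complex effect is set to zero here.

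- Intervention-arm design effect: DE = 1 + (m − 1) × ICC, with m = 5.
- SE factor, arm difference with equal arms: √((DE + 1)/2).
- SE factor, within-intervention-arm change: √DE, where the ICC is that of the change.
- Type I error: 2 × (1 − Φ(1.96 / factor)).

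| ICC | DE | SE factor, between arms | Type I, between | SE factor, within arm | Type I, within |
|---|---|---|---|---|---|
| 0.02 | 1.08 | 1.020 | 5.5% | 1.039 | 5.9% |
| 0.05 | 1.20 | 1.049 | 6.2% | 1.095 | 7.4% |
| 0.10 | 1.40 | 1.095 | 7.4% | 1.183 | 9.8% |

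A simulation under the null (20,000 runs, four complexes of 80, SD 15, groups of five) gave between-arm type I error of 5.9% at ICC 0.05 and 7.0% at 0.10, close to the formula.

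**After dropout.** With 30% lost, 5 × 0.7 = 3.5 members remain per group. DE becomes 1.05 to 1.25, between-arm type I error 5.3% to 6.5%, and within-arm error 5.6% to 8.0%. Power for 5.4 mmHg with 160 × 0.7 = 112 completers per arm is 76.9% if all are independent. It falls to 75.8%, 74.3% and 71.9% at ICC 0.02, 0.05 and 0.10. If groups stayed at five it would be 75.2%, 72.9% and 69.1%.

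**Compared with the complex level.** With 320/4 = 80 participants per complex and an assumed complex ICC of 0.02, the design effect is 1 + 79 × 0.02 = 2.58 and the SE factor √2.58 = 1.61. The simulated t test then rejects in 22.3% of null trials. Adding peer-group ICC 0.05 raises that to 23.3%.

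**Does a complex-level analysis leave the peer-group part behind?** Take peer groups as nested in complexes, with 80/5 = 16 groups in each intervention complex. The variance of an intervention-complex mean is σ²(complex) + σ²(group)/16 + σ²(residual)/80. At complex ICC 0 and peer ICC 0.05:

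- Intervention: 11.25/16 + 213.75/80 = 3.375.
- Control: 225/80 = 2.8125.
- SE of the arm difference: √((3.375 + 2.8125)/2) = 1.759, against the naive √2.8125 = 1.677.

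The observed spread of complex means therefore already contains the peer-group term. In the simulation, a t test on complex means with 2 degrees of freedom had type I error of 4.7% to 5.1% for peer ICC 0 to 0.20. Its root-mean-square SE matched the true SE: 1.76 v 1.75 at complex ICC 0 and peer ICC 0.05, and 2.75 v 2.76 at 0.02 and 0.05. A random complex intercept referred to 2 degrees of freedom was conservative, rejecting in at most 0.4% of these runs.

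**The case against.** The strongest objection is that this is a small increment to a larger defect. That stands: at complex ICC 0.02, peer-group ICC 0.05 adds about one percentage point to an error rate already near 22%. The 5.5% to 7.4% range describes peer-group correlation alone and must be presented so.

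A reader might go further and infer that peer-group correlation would survive a term for housing complex, leaving intervention-arm precision overstated even after that repair. The documents do not support this. They contain no complex term to criticise, and groups formed among neighbours are most naturally nested in complexes, so a complex-level comparison carries their variance. A random complex intercept with normal critical values does over-reject at complex ICC 0.02, but it does so at 11.7% with no peer-group correlation and 11.9% at peer ICC 0.05; the cause is having only four complexes. At smaller complex ICCs the peer groups add a little more with such critical values: from 8.5% to 10.5% at complex ICC 0.01 as peer ICC goes from 0 to 0.20. Small-sample degrees of freedom deal with this. A fixed complex effect would be confounded with arm.

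Two further inferences fail. Stronger peer support need not mean a higher ICC, because uniform support shifts the arm mean without adding variation between groups. Nor does the shared monitor create common measurement error in the primary outcome: the groups receive the HEM-7111, while the Blood pressure measurement section names the HEM-7211 for outcomes.

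It could also be said that a condensed article leaves such detail to an analysis plan. That does not remove the point, because the article itself names analyses that assume independence.

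**Conclusion.** The point holds for the analyses as written. Correlation within peer groups is confined to the intervention arm and is ignored. For an assumed ICC of 0.02 to 0.10 and groups of five, the SE is too small by a factor of 1.02 to 1.10 between arms and 1.04 to 1.18 for change within the intervention arm. Type I error is about 5.5% to 7.4% and 5.9% to 9.8% respectively, and less if groups shrink through dropout.

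This rests on an ICC that the documents do not give, on no complex effect in those figures, and on the inference that peer groups are nested in complexes. It is worth correcting but is secondary to the ignored clustering by the four randomised complexes. Once the arm comparison is made validly at that level, no separate peer-group term is needed for its type I error. The term still matters for any individual-level or within-arm analysis that is kept.

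**What to change.** 1. First base the arm comparison on the randomised unit: complex-level summaries, or a random complex effect with small-sample degrees of freedom. With two complexes per arm this leaves 2 degrees of freedom and much wider intervals; that cost belongs to the complex-level problem.
2. Record a peer-group identifier for every intervention participant when the groups are formed. It is one variable, and may be hard to rebuild later.
3. Wherever an individual-level or within-arm analysis of blood pressure, diet, activity or fitness is kept, add a peer-group random effect in the intervention arm only. For within-arm change, standard errors clustered on peer group would also do.
4. Report the estimated peer-group ICC, which is useful for planning any replication.

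The cost of items 2 to 4 is one identifier, one model term and slightly wider confidence intervals.
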